#### **5.5.2 Handling of Subject Withdrawals or Subject Discontinuation of Study Intervention**

Subjects who are withdrawn from the study, either through voluntary discontinuation, for failure to complete study questionnaires, or by decision of the principal investigator for reasons enumerated above, will be recorded as terminated. They will be sent a letter confirming their early termination from the study and will no longer be

followed. They will not be sent any further follow-up questionnaires or brought back for a follow-up visit & MRI (if applicable).

If a subject is withdrawn due to an SAE or other medical condition that precludes their continuation in the study, the study or site PI will call the subject to discuss and ensure appropriate medical treatment or follow up is arranged.

The study sample size has been calculated to allow for attrition due to early withdrawal or discontinuation.

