## **4 STUDY DESIGN**

### **4.1 Primary Study**

This is an unblinded, multi-center, pragmatic randomized controlled clinical trial of operative versus non-operative treatments for atraumatic rotator cuff tears. A sample size of 700 patients will be enrolled with approximately equal numbers of patients randomized to operative treatment (surgery + post-op physical therapy) and non-operative treatment (physical therapy only without surgery). Both treatments are current standards of care. The duration of enrollment is expected to last approximately 3.5 years. For the main study and analysis, a 12-month follow-up is needed, with the duration of the primary study lasting for approximately 5 years.

Upon enrollment at baseline, patients will fill out study questionnaires, undergo a brief physical examination, and, if applicable, have a research MRI. Follow-up for the primary study will be performed via questionnaires at 3, 6, and 12 months.

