#### **5.5.1 Reasons for Withdrawal**

Subjects are free to withdraw from participation in the study at any time upon request.

An investigator may terminate a subject's participation in the study if:

- Any serious adverse event (SAE) or other medical condition or situation occurs such that the subject cannot continue or continued participation in the study would not be in the best interest of the subject.
- The subject is deceased.
- The subject does not complete any follow-up questionnaires in the first year.
- The subject does not complete annual follow-up questionnaires two years in a row for the sub-study.
- The study ends earlier than anticipated.

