#### **9.1.3 Serious Adverse Events (SAEs)**

SAEs for this trial include:

- Death
- Event requiring hospitalization (in-patient admission) related to treatment

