### 12.2 Final Analysis Plan

**Overview:** We are planning a trial where patients will be randomly assigned in equal proportion to operative or non-operative care.

**Primary Endpoint:** The primary outcome measure is SPADI, and the primary endpoint is the change in SPADI at 12 months relative to baseline. SPADI is measured on a scale of zero to 100, with lower scores for better outcomes. SPADI is a reliable and valid measure of shoulder function.

**Secondary Endpoint(s):** ASES-SF, cross-sectionally and longitudinally over time.

**Analysis Population:** We define the intent-to-treat (ITT) population as the group of patients randomized to a treatment arm regardless of any other consideration.

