#### 12.2.1 Primary Analysis

The primary analysis will be conducted on the intent-to-treat (ITT) population as defined above. The distribution of 12-month change in SPADI, stratified by treatment

arm, will be summarized graphically with histograms, boxplots, and plots of CDFs as appropriate. Our primary analysis for testing the 3 specific hypothesis in section 12.1 will be conducted in the context of a mixed model. That model is,

$$y_{ij} = \beta_0 + \beta_1 I_{\{TRT_i=op\}} + \beta_2 t_{ij} + \beta_3 I_{\{TRT_i=op\}} t_{ij} + \beta_4 (tearsize_i) + \beta_5 (age_i) + \beta_6 (I_{\{TRT_i=op\}} * tearsize_i) + \beta_7 (I_{\{TRT_i=op\}} * age_i) + u_i + e_{ij}$$

where  $y_{ij}$  represents the change in SPADI from baseline for participant  $i = 1, \dots, n$  at time  $j = 3, 6, 12$  months who was assigned to management arm  $TRT_i$  ( $I_{\{TRT_i=op\}} = 1$  if participant  $i$  is on the Operative arm and 0 otherwise).  $\beta_0$  is the intercept,  $\beta_3$  is differential change in SPADI score over time due to treatment (i.e., the treatment effect over time; assumed linear here but it will be modeled flexibly as needed),  $\beta_4$  and  $\beta_5$  are the effects of tear size and age at the beginning of treatment, and  $\beta_6$  and  $\beta_7$  are the tear size and age interactions with treatment that potentially will help identify those patients most likely benefit from therapy. The first 8 terms represent fixed effects. The last 2 terms represent a patient specific random intercept to model the effects of study site and residual error, respectively. The estimate of interest from this longitudinal model is the predicted differential in 12-month SPADI change ( $\Delta\Delta SPADI_{12}$ ; 1st  $\Delta$  is for treatment change, 2nd  $\Delta$  is for 12-month change), which is typically estimated as a contrast or difference in predicted 12-month SPADI change.

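### Termination for an SAE or medical condition also stops the questionnaires, so the 12-month SPADI is lost by rule for patients who could still answer

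*Protocol*

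**What the plan says.** Section 5.5.1 lists the grounds on which an investigator may end a subject's participation. One is: "Any serious adverse event (SAE) or other medical condition or situation occurs such that the subject cannot continue". The same item also allows termination when continuing would not serve the subject's best interest. The power is discretionary.

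Section 5.5.2 treats all terminated subjects alike, whatever the ground. They are recorded as terminated and not followed further: "They will not be sent any further follow-up questionnaires or brought back for a follow-up visit & MRI (if applicable". After a medical termination the only further contact described is a call from an investigator about medical care.

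Section 4.1 gives the source of outcome data: "Follow-up for the primary study will be performed via questionnaires at 3, 6, and 12 months". Section 12.2 states that "the primary endpoint is the change in SPADI at 12 months relative to baseline". The same section defines the intent-to-treat (ITT) population as "the group of patients randomized to a treatment arm regardless of any other consideration", section 12.2.1 applies that population to the primary analysis, and section 12.4 describes the primary model as strictly intent-to-treat.

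Other departures from plan do not end follow-up. Subjects who cross over stay in the study (5.3.2). Subjects whose central MRI read shows no tear, or a tear above 4 cm, are not withdrawn (6.5.4).

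**The concern.** The rule joins two separate things: leaving the assigned treatment or the study's care pathway, and ending data collection. After randomization the main study asks little of a subject beyond questionnaires, on paper or online. Both treatments are standard care. A medical event that ends treatment therefore need not end the reporting of SPADI.

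The loss may also be selective. Section 9.1.3 counts as SAEs death and "Event requiring hospitalization (in-patient admission) related to treatment". Section 2.4.1 lists bleeding, infection, clot, readmission and anesthesia complications for surgery. For physical therapy it lists pain, lack of improvement and frozen shoulder. Non-fatal SAEs can therefore be expected more often after surgery. The trial is unblinded, and the investigator who decides on termination knows the arm. If terminated patients recover less well than the rest of their arm, leaving them out makes surgery look somewhat better than it is, which is the direction of Hypothesis 1.

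**Working it through.** **Inputs from the protocol.** 350 per group and two-sided alpha 0.05 (12.3.3); a 10-point SPADI difference as the smallest meaningful change (12.3.2); preliminary 12-month changes of −12.3 (SD 21.55, n=45) non-operative and −40.6 (SD 19.14, n=27) for the other group, read here as operative (12.3.1).

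**The plan's own figure first.** Pooled SD = √[(44 × 21.55² + 26 × 19.14²)/70] = 20.69. For 90% power at 10 points the normal approximation gives 90 per group. The noncentral t gives 91 (power 90.03%), which is the plan's figure for the unadjusted t-test.

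**Precision is not the issue.** SE of the arm difference = 20.69 × √(2/350) = 1.56. Power for 10 points exceeds 99.9% at 350 per group and still does at 315 (10% lost). The attrition allowance mentioned in 5.5.2 protects power. It does not correct selective loss.

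**Bias.** Let p be the share of the operative arm terminated who could have answered, and D their SPADI-change deficit against the rest of that arm. If they are simply absent, the operative mean is too favourable by p × D. Equal loss with equal deficit in the other arm would cancel this; the table assumes none there. With true difference zero, the false-positive rate is 1 − Φ(1.96 − b/SE) + Φ(−1.96 − b/SE), where b = p × D.

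The protocol gives neither p nor D, so both are assumed. D = 28.3 is the full preliminary contrast (40.6 − 12.3); D = 20 is a smaller value.

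| p | Patients of 350 | D = 20: bias (in SE; false-positive rate) | D = 28.3: bias (in SE; false-positive rate) |
|---|---|---|---|
| 1% | 3.5 | 0.20 (0.13; 5.2%) | 0.28 (0.18; 5.4%) |
| 2% | 7 | 0.40 (0.26; 5.8%) | 0.57 (0.36; 6.5%) |
| 5% | 17.5 | 1.00 (0.64; 9.8%) | 1.42 (0.90; 14.8%) |
| 10% | 35 | 2.00 (1.28; 24.9%) | 2.83 (1.81; 44.0%) |

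The 10% row borrows the SAE ceiling from section 9.5 as an extreme. It supposes that one operative patient in ten is terminated.

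**Two cautions.** The preliminary means do not reconcile with the stated overall mean of −16.7: (45 × −12.3 + 27 × −40.6)/72 = −22.9. So 28.3 is a rough upper value. And if there were no treatment difference and both arms improved by 12.3, a terminated patient with no change would have D = 12.3 only, giving 0.25 points at 2% and 0.62 at 5%.

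**The case against.** A reader might infer that the patients with the worst results, mostly surgical, are systematically removed. The documents do not support that.

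- Termination is permitted, not required, and only when the subject cannot continue or continuing is against the subject's interest. A patient admitted with an infection who recovers need not be terminated.
- Death counts as an SAE without limit of cause or arm, and leaves no 12-month SPADI under any rule. The ground of another medical condition is not specific to an arm either.
- Section 2.4.1 supports more treatment-related admissions after surgery and nothing beyond that. Crossovers to surgery are analysed in the non-operative arm, and section 9.5 calls the surgery very low risk. An SAE is not a SPADI score.

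A larger figure is also tempting: give terminated patients zero true change and suppose the model credits them with −40.6, so the bias is p × 40.6, or 0.8 to 2.0 points at p of 2–5%. That is an upper bound. It ignores 3- and 6-month scores already returned, which stay in the mixed model. Setting it against a 10-point effect mixes scales too: on the same preliminary figures the contrast is 28.3 points, so the bias is 3–7% of it.

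Nor does the rule contradict the ITT definition. Terminated patients stay in that population with a missing outcome. Section 12.4 names analyses under missing-at-random and missing-not-at-random assumptions, whose detail may sit in an analysis plan that is not at hand.

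All of this stands and limits the point. It does not remove it. The best-interest ground reaches patients who can still answer, and a patient terminated before month 3 has no post-baseline value and contributes nothing to the change-score model. A sensitivity analysis is a weaker remedy than collecting the score.

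**Conclusion.** The point holds in a limited form. Sections 5.5.1 and 5.5.2 together create avoidable missing values in the primary endpoint, by a discretionary decision in an unblinded trial, and the loss is plausibly related to arm and outcome.

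The likely size is small: about 0.2–0.6 points at 1–2% of the operative arm terminated, or 0.13–0.36 standard errors. This assumes a deficit of 20–28.3 points, no offsetting loss in the non-operative arm and no use of earlier scores. Every value in the table is below the 10-point threshold, so the rule is unlikely to explain a clinically meaningful difference by itself. It could matter near the null: a bias of 1 point would raise the false-positive rate to about 10%, but at a 20-point deficit that needs about 5% terminated. The documents support neither that rate nor a claim that the lost patients are the worst surgical outcomes.

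The change is still worth making, because it is cheap and a questionnaire that was never sent cannot be recovered.

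**What to change.** Amend sections 5.5.1 and 5.5.2 so that an SAE or other medical condition does not by itself end questionnaire follow-up through month 12. Keep sending the 3-, 6- and 12-month questionnaires unless the subject dies, withdraws consent for follow-up, or is unable to complete them. The last ground covers incapacity. Record which of these applied and when, so that the missing-data analyses can use the reason.

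This alters data collection only and leaves clinical care and treatment decisions as they are. The cost is a short amendment with IRB review and a few more questionnaires through the existing system: on the assumptions above, about 4 to 7 operative patients, each with at most three questionnaires.

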## **5.6 Premature Termination or Suspension of Study**

The study may be suspended or prematurely terminated if there is sufficient reason or cause. Per the Data & Safety Monitoring Committee (DSMC) charter, the DSMC will monitor progress of the trial and determine any actions related to suspension or termination of the trial. (See Supplemental Materials)

Written notification, documenting the reason for study suspension or termination, will be provided by the suspending or terminating party to the investigator, funding agency, and regulatory authorities. If the study is prematurely terminated or suspended, the principal investigator will promptly inform the IRB and will provide the reason(s) for the termination or suspension.

## 6 STUDY INTERVENTION

### 6.1 Study Procedural Intervention(s) Description

Patients will be randomized to either an operative or non-operative treatment regimen. Non-operative and operative interventions performed for this study are consistent with routine clinical standards of care for rotator cuff tears.

#### 6.1.1 *Non-operative Intervention*

Subjects randomized to the non-operative arm of the study will follow a standardized non-operative rehabilitation program. They will not undergo rotator cuff surgery (unless subjects cross over).

**Non-operative Rehabilitation Regimen:** Subjects randomized to the non-operative arm of the study will follow a prescribed (approximately 3-month) physical therapy and home exercise program to strengthen and stabilize the shoulder muscles. A standardized, non-operative rehabilitation protocol (see Supplemental Materials) has been developed for this trial with extensive input from our team of clinicians, researchers, and expert consultants. Subjects may continue physical therapy beyond 3 months as prescribed/deemed appropriate by their treating clinicians.

#### 6.1.2 *Operative Intervention*

Subjects randomized to the operative arm of the study will undergo surgery to debride or repair the rotator cuff tear and then follow a standardized post-operative rehabilitation program.

**Surgery:** The subject's attending surgeon will perform a rotator cuff repair or debridement based on the evidence-based surgical protocol (see Supplemental Materials) developed for this trial. This protocol has been developed to maximize the potential for rotator cuff tear repair healing and to reduce the variables that could affect surgical outcomes.

Information will be collected on the specific surgical techniques used, such as number of anchors and type of repair (e.g., single row, double row, transosseous, or transtendinous). Any concomitant procedures such as subacromial decompression and acromioclavicular joint resection will also be noted. (See Appendix, Surgery Report Form.)

**Post-Operative Rehabilitation Regimen:** Following surgery, subjects will follow a prescribed (approximately 4-month) physical therapy and home exercise program to strengthen and stabilize the shoulder muscles. A standardized, post-operative rehabilitation protocol (see Supplemental Materials) has been

developed for this trial with extensive input from our team of clinicians, researchers, and expert consultants. Subjects may continue physical therapy beyond 4 months as prescribed/deemed appropriate by their treating clinicians.

The post-operative rehabilitation regimen is similar to the one that will be followed for non-operative rehabilitation. The main difference between the two intervention arms is the rotator cuff surgery.

## **6.2 Concomitant Medications/Treatments**

Subjects will be able to take analgesic medications or have shoulder injections, since it would not be ethical to restrict the use of these interventions. Use of co-interventions will be recorded in follow-up questionnaires completed by the subject.

## **6.3 Administration of Procedural Intervention**

Interventions will be standardized to the extent this is possible. Standardized protocols have been developed for surgery, as well as for both non-operative and post-operative rehabilitation regimens, and will be disseminated to treating clinicians.

### **6.3.1 Surgery**

Study surgeons at each recruiting site will administer the surgical rotator cuff repair/debridement for those subjects in the operative arm of the study recruited from their site. Surgery should be scheduled to occur within 8 weeks after randomization to the operative treatment arm. If surgery occurs later than 8 weeks after randomization, it will be considered a protocol deviation.

### **6.3.2 Physical Therapy**

Local physical therapists will administer the post-operative and non-operative rehabilitation regimens for subjects in both arms of the study. Site coordinators will assist in referring subjects to a physical therapist at a location that is convenient for them. Preferably, this should be a physical therapist familiar with the study or a physical therapist at one of the designated local PT networks for each site, whenever feasible. Subjects may also utilize any physical therapist of their choice.

Physical therapy should begin within 8 weeks after randomization to the non-operative treatment arm or within 8 weeks following surgery, if in the operative arm. If physical therapy begins later than this time period after either assignment to the non-operative arm or undergoing surgery, it will be considered a protocol deviation.

**Non-Operative Physical Therapy:** The duration of the non-operative physical therapy program will be approximately 3 months, with subjects attending physical therapy 1-2 times a week on average, for a total of approximately 12-24 visits.

The treatment stages of the non-operative rehabilitation protocol are goal/performance based. Non-operative subjects who make rapid progress may be advanced to the next stage of the rehabilitation treatment protocol if they meet the criteria to do so and may be discharged from physical therapy earlier than 3 months as appropriate.

**Post-operative Physical Therapy:** The duration of the post-operative physical therapy program will be approximately 4 months, with subjects attending physical therapy 1-2 times a week on average, for a total of approximately 16-32 visits.

The treatment stages of the post-operative rehabilitation protocol are pegged to specific timeframes following surgery. Subjects in the operative arm who meet treatment goals for a given stage early should NOT be advanced to the next stage ahead of schedule, in order to allow proper healing of their shoulder post-op. Rather, the interval between physical therapy visits should be increased as appropriate.

The actual number and frequency of physical therapy visits will vary over the course of treatment and by subject, based on individual progress and needs.

### **6.3.3 Home Exercise Program**

Subjects themselves will be responsible for attending scheduled physical therapy treatments and adhering to the home exercise program as prescribed by their physical therapist until discharged from physical therapy.

To be considered compliant with the rehabilitation regimen for either arm of the study, subjects are expected to attend physical therapy &/or complete their home program exercises a total of at least three times each week. The three times can be any combination of the two (e.g., 2 physical therapy visits + 1 day of home exercises, 1 physical therapy visit + 2 days of home exercises, and so on).

## **6.4 Procedures for Training of Clinicians on Procedural Intervention**

### **6.4.1 Treating Surgeons**

All study surgeons will be briefed on the standardized surgical protocol that has been developed with physician input and will follow the surgical protocol.

#### **6.4.2 Treating Physical Therapists**

To ensure that treating physical therapists – many of whom will be otherwise unacquainted with the study – are aware of the subject's participation in and the requirements of the study, each recruiting site will have a designated Lead Physical Therapist. His/her job will be to contact the treating physical therapist for all subjects recruited from their site as soon as possible after treating physical therapist contact information is obtained, ideally within 2-3 weeks *after randomization* (for the non-operative arm) or within 2-3 weeks *after surgery* (for the operative arm).

The site Lead Physical Therapist will ensure that the treating physical therapist receives a copy of the appropriate rehabilitation protocol (operative or non-operative), will explain the details of the study, will stress the importance of protocol adherence, and will answer any questions the treating physical therapist has regarding the treatment protocol. Treating physical therapists will be encouraged to call their Lead Physical Therapist at any time they have a question or concern during the course of treatment.

#### **6.4.3 Subjects**

Subjects will be provided with a Rotator Cuff Home Exercise Program (see Appendix) that contains various exercises which may be assigned to them during their home exercise program. They will be instructed to bring this brochure with them to each physical therapy visit so that their physical therapist can update the assignment of exercises and the set/reps, frequency, etc. for each exercise at each visit. Exercises that no longer need to be performed will be crossed off as finished/discharged. Proper use of the patient exercise brochure will help to ensure that subjects know exactly which exercises they should be doing (in what amount and with what frequency) at any given time and will promote compliance with the home program.

#### **6.4.4 Research Staff**

Research staff will not administer treatment interventions but will be trained by their site physical therapist and provided written instructions on how to perform a physical exam in clinic to measure the strength of both shoulders for each subject (using a dynamometer). In some cases, a physician may designate staff member (e.g., a Physician's Assistant or qualified delegate) to perform the range of motion portion of the physical exam.

